**5. What is your plan for secondary variable analysis?**

The same statistical approach to primary variable analysis will be conducted.

Bivariate regression analysis to understand the relationship between blood and urine MPs to inform future studies which tissue to collect from. Currently, it is not understood how MPs collected in the blood relate to MPs collected in the urine.

**6. Have you been working with a statistician in designing this protocol? NO**

**7. Will data from multiple sites be combined during analysis? N/A**

# Biomedical Research

**1. What will be done in this protocol?**

This study will determine cardiorespiratory fitness (VO2max test, 6-minute walk test), body composition analysis, blood chemistry during a mixed-meal tolerance test, vascular function (pulse wave velocity and augmentation index), immune cell phenotyping, and adipose tissue gene expression of inflammatory markers before and after exercise and/or diet compared with control both before and after bariatric surgery. Below describes each assessment.

**2. List the procedures, in bullet form, that will be done for RESEARCH PURPOSES as stipulated in this protocol.**

**** All procedures/assessments are being done for research purposes only****

Each subject will visit UVA for around 15 visits that include: the CRU 5 times – one preliminary screening visit, one visit to obtain baseline fitness and anthropometric data, and one visit per experimental condition (described below), up to 8 exercise sessions in Memorial Gymnasium with exercise physiologists, and/or about 4 visits for dietary pick up at Memorial Gymnasium or the CRU (which ever is more convenient to the subject).

**Outpatient Screening Visit #1**: **(this visit will last about 2 hours)*:***

- Potential subjects will report to the CRU at least 12-hours in the post-absorptive state (nothing but water after ~7-8 PM the night before). Participants will be asked to report to the CRU between 7 and 8 AM (i.e., 12 hours after their last meal).
- Participants will be consented and then carefully queried to ensure that they meet the pre-screening eligibility criteria as described in the inclusion/exclusion criteria using the Screening Questionnaire (that includes the Physical Activity Readiness Questionnaire or PAR-Q: This is a checklist of 9 questions ensuring subjects can participate in cardiovascular exercise. This questionnaire is routinely used by the American College of Sports Medicine to assess safety for exercise in at risk populations).
- Eligible persons will provide written informed consent prior to participating in any

experimental procedures.

- Vital signs, height and weight will be measured.
- Prior to testing, A needle will be inserted into a vein in either the forearm or back of your hand to take a blood sample. .
- Blood will be drawn for CBC, liver function tests, HbA1c, HCT for women > 36%, Men >38%, BUN, fasting blood glucose and fasting lipid profile. For females, a serum HCG will be drawn.

This visit will take approximately 2 hours and approximately 9 cc of blood will be drawn for men and 12cc for women.

**Subjects meeting the above criteria will be continue on and attend the 2^nd^ study test visit. This test will be conducted on a separate date and be within 1 month after the above screening visit):**

***Phase 2: SCREENING AND STUDY TESTING PROCEEDURES***

**Study Test Visit 2 (this visit will last about 2 hours)*:***

**Subjects must fast (not eat) for 4 hours before this visit.**

The second screening visit will start with a:

- Review of the subject’s medical history
- Physical exam and vital signs (blood pressure, heart rate and resting electrocardiogram)
- If subjects are women who are able to bear a child, they will have a urine pregnancy test that must be negative in order to participate.

The purpose of the physical exam is to determine if subjects are eligible for the exercise portion of the study and that it is safe for them to participate. The pregnancy test must be negative in order for the subjects to participate. If subjects continue to qualify for the study the remainder of the visit will involve the study procedures described below:

**A. Body Composition**:

- Subjects must be fasting for at least 4 hours before this procedure.
- Subjects weight will be measured without shoes and while wearing minimal clothing.
- Subjects waist and hip circumference ratio will be obtained with a tape measure to determine how much fat is located in the central part of the body.
- We will measure the total amount of fat and muscle in your body with the BodPod® in the Exercise Physiology Core Lab.
- We will provide a swimsuit and swim cap for you to wear during this procedure to help standardize your results.  The swimsuit and swim cap are provided to get accurate results.  You will not get wet at anytime during this measurement.
- The research team will also measure the regional amount of fat and skeletal muscle in the subjects’ bodies with the InBody®. This testing will be conducted in Memorial Gymnasium and a team member will walk the subjects over to the location.
- The InBody® procedure requires subjects to stand on a platform and hold a handrail. This test using a low-level, safe, electrical current through the body. The current travels at a different rate through the various body tissues, which then allows a calculation of body fat and muscle.
- The entire InBody® procedure takes approximately 15 minutes.
- Weight will also be obtained on a Bod Pod scale without shoes and while wearing minimal clothing in the Exercise Physiology Core Lab.
- Body composition (%body fat) will be determined by air displacement plethysmography. This requires that the participant sit in a 750-liter volume, dual chamber fiberglass shell and rest quietly for a few minutes. The Bod Pod has a window that enables the participant to see out of the chamber at all times, thus minimizing the risk of claustrophobia. Bod Pod measurements take approximately 5-7 minutes total time to complete.

**B. Treadmill or cycle ergometer exercise testing for cardiovascular fitness (i.e. VO2max)**:

- Subjects will be asked to perform a maximal treadmill or cycle ergometer exercise test in the Exercise Physiology Core Laboratory in the School of Medicine. The treadmill test will begin with low speed on the treadmill, and the speed and/or elevation will increase gradually every 2 minutes. You will complete the treadmill test if undergoing bariatric surgery. However, if you are not undergoing bariatric surgery, then you will perform the cycle ergometer test. The cycle ergometer test will begin with low resistance on the bicycle wheel, and the resistance will increase gradually every 3 minutes. Subjects will be asked to go as long as they can, that is, until they feel exhausted.
- During the test, subjects will have continuous electrocardiogram (ECG) heart monitoring and blood pressure monitoring by professionally qualified exercise physiologists of the Exercise Physiology Core Lab. All testing procedures follow the American College of Sports Medicine Guidelines.
- During exercise testing researchers will also measure the subjects’ metabolic rate, a measure of the amount of energy it takes to burn calories. During exercise subjects will wear a facemask that is connected to a special device (metabolic cart) that measures subjects’ exhaled carbon dioxide (CO_2_) and oxygen. These measurements are then used to calculate the amount of calories they burn.
- During the exercise test, the subject will wear a mask over their nose and mouth. This allows the researchers to measure how much oxygen the subject is using and will tell the researchers what the subject’s fitness level is.
- The visit ends after the subject completes the exercise test. The subject will receive the results of their test after the completion of the study.
- Subjects will also be provided with an **accelerometer** and instructions on how to use the accelerometer. The accelerometer is a small device, similar to a pedometer, which is worn on the belt and records the amount of activity performed. Data will be downloaded from it on a weekly basis.

**C. Timed Walk Test (ie. 6-Minute Walk Test):**

- Subjects will be asked to complete a timed 6-minute walk test (6-MWT) on a reserved basketball court in Memorial Gymnasium under supervision of study personnel after physician clearance. Subjects will be instructed to wear comfortable shoes and can take medications as usual.
- The basketball court will be clearly marked every 3 meters for 30 meters total.
- Monitoring equipment used include a stop watch, heart rate monitor, blood pressure cuff, and Borg scale for evaluation of perceived exertion. Prior to the walk test, resting heart rate, blood pressure, and perceived exertion will be measured to ensure the subject is within the American College of Sports Medicine’s recommendations for exercise.
- Individuals will be instructed to walk as quickly as they can up and down the basketball court for 6 minutes so that they cover as much ground as possible. Subjects will be instructed that they can use ambulatory devices (ie. cane or walker) and can stop to take rests as needed.
- Subjects will be updated on the time remaining every minute.
- Immediately at the end of the test and blood pressure, heart rate, and perceived exertion will be measured. It will be marked where the subject stopped after 6 minutes and total distance traveled will be recorded.
- Heart rate and blood pressure will be measured periodically until levels return to resting value. At this point the subject will be allowed to leave the facility.

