**2. List the criteria for exclusion**

- Currently participating in exercise training: >30 min. of physical activity per day, >2 days/week)
- Cigarette smoking (presently or in the past 6 months), drug or alcohol abuse
- Pregnancy or breastfeeding
- History of congestive heart failure, ischemic heart disease, severe pulmonary disease.
- History of cancer (within 5 years)
- Diagnosed as insulin-dependent diabetes.
- Change in psychotropic medication dosage in past six weeks
- AST or ALT > 3 times normal range
- Currently involved in any active weight loss treatment program (other than self-directed attempt at calorie restricting diet) or lean patients (BMI <29 kg/m^2^).
- Current purging behavior occurring > once a week over the past six weeks (self-induced vomiting for weight control purposes, laxative or diuretic abuse)
- Revisional bariatric procedures including a RYGB reversal to a SG or a LAGB revision to a SG or RYGB if the band has been adjusted in ≤ 1 year.
- Active psychotic illness, including bipolar affective disorders.
- Evidence of current suicidality or homicidality
- Conditions associated with significant cognitive dysfunction (e.g. dementia) or medical instability that puts the participant at risk
- Contraindication to exercise (severe/uncontrolled CVD; inability to walk 2 blocks, bone or joint problems )
- Allergy to “caine” family drugs (e.g. lidocaine).
- Currently taking active weight suppression medication (e.g. phentermine,bupropion SR, topiramate).
- On medication known to cause substantial weight gain (e.g. atypical antipsychotics such as olanzapine, sodium valproate, steroid therapy). This would not include medications commonly used in this population that usually result in only mild weight loss (e.g. SSRIs).

**3. List any restrictions on use of other drugs or treatments**.

- Medication or food supplement known/thought to affect insulin sensitivity or endothelial function (TZDs, sufonylureas, biguanides, alpha-glucosidase inhibitors, phosphodiesterase inhibitors, beta-blockers, alpha-blockers, ACE-inhibitors, ARB’s, fibrates, glucocorticoids, fish oil, allopurinol, Vitamin E, Vitamin C).
- Subjects cannot ingest medications or food supplements (e.g. statins, dietary supplements, etc.) 24 hours before testing.
- Subjects cannot drink alcohol 24 hours before testing.
- Subjects cannot eat or drink foods that contain caffeine 24 hours before testing.

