**Study Testing Visits 3-6: (each visit will last about 6 hours):**

**The following information will be provided to the subject**

- While the subject is in the study, they will be asked to maintain their normal physical activity level.
- Subjects will be asked to follow a special diet for 1 day before study testing visits 3, 5 and 7. The diet will require subjects to eat at least 200 grams of carbohydrate each day while limiting the amount of fat ingested. Subjects will be given a chart to help record their carbohydrate and food intake and must return the chart on the day of their admission.
- **Subjects must not drink alcoholic or caffeinated beverages for 24 hours before the study testing visit begins** (i.e. after 7am the day before the test).
- **Subjects** **must not use allergy or pain-related medicines (over-the-counter or prescription**) for at least 5 days prior to each admission.
- **Subjects must not use antibiotics for 3-4 weeks before study testing visits.** If subjects have been prescribed an antibiotic 3-4 weeks before the study or are prescribed an antibiotic during the study they should inform the investigators. This may result in an inability to collect fecal matter for gut microbiota analysis.
- **Subjects must not use statins, glucose lowering medication, or antioxidant dietary supplements 24 hours before the study testing.**
- **Subjects must not perform any vigorous exercise for 48 hours prior to each test day**.
- The tests must be performed in the fasted state, so subjects may not eat or drink anything (except water) after about 7pm the night before.
- Subjects will be asked to report to the CRU by approximately 7:00am on the morning of each test.
- If a subject is a pre-menopausal woman, they will be asked to report to the CRU to provide a urine sample for a pregnancy test. The test must be negative in order for them to continue their participation.

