**Study Schedule Visit Overview for Bariatric Patients**

| **Study Visit** | **Screening Visit 1** | **Screening Visit 2^** | **Pre-Test Visit 3** | **Exercise Training 1-2 d/wk***  **Visits 4-11** | **Post-Intervention Testing**  **Visit 4**  **(or Visit 12)^** | **Bariatric Surgery**  **Visit 5**  **(or Visit 13)** | **Post- Bariatric Surgery Testing**  **Visit 6**  **(or Visit 14)^** |
| --- | --- | --- | --- | --- | --- | --- | --- |
| Consent | X |  |  |  |  |  |  |
| Blood Draw | X |  | X |  | X |  | X |
| History and Physical |  | X | X |  | X |  |  |
| Urine Collection (Nitrogen Analysis) |  |  | X |  | X |  | X |
| Stool Collection  (Gut Bacteria) |  |  | X |  | X |  | X |
| VO2peak (Treadmill testing) |  | X |  |  | X |  | X |
| Timed Walk Test (6-MWT) |  | X |  |  | X |  | X |
| Body Fat measurement |  | X |  |  | X |  | X |
| Adipose Biopsy |  |  | X |  |  | X |  |
| MMTT |  |  | X |  | X |  | X |
| Indirect Calorimetry |  |  | X |  | X |  | X |
| Blood Pressure, AI and PWV tests |  |  | X |  | X |  | X |
| Diet Record |  |  | X |  | X |  | X |
| Appetite Questions |  |  | X |  | X |  | X |
| Quality of Life Questions |  |  | X |  | X |  | X |
| Laval Questionnaire |  |  | X |  | X |  | X |
| Accelerometer |  | X |  |  | X |  | X |
| Heart Rate Monitors |  |  |  | X |  |  |  |
| Urine Pregnancy Test (women) |  | X | X |  | X |  | X |

Note: Subjects will be match paired to the group for pre-operative treatment. ^Visit 2 is designed to be performed in 1 day. However, if time does not permit this day may be separated in to 2 visits to accommodate needs. Also, we perform fitness and body fat tests within 3 days post blood work to minimize any time constraint involved in blood work tests. ** Exercise Training will be performed at UVA in Memorial Gymnasium and fully supervised by an exercise physiologist. Heart rate monitors are to be worn when at home exercising as well.

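### The protocol does not settle which medication rule governs the repeat 6-minute walk test, so some subjects could be tested with medication at baseline and without it at follow-up

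*Protocol*

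**What the plan says.** Three instructions in the protocol bear on medication before a test.

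- **Study Test Visit 2, part C (Timed Walk Test):** "Subjects will be instructed to wear comfortable shoes and can take medications as usual".
- **Inclusion/Exclusion Criteria, item 3 (restrictions on other drugs or treatments):** "Subjects cannot ingest medications or food supplements (e.g. statins, dietary supplements, etc.) 24 hours before testing". No test or visit is exempted, and the word for the occasion is not defined.
- **Study Testing Visits 3-6:** "Subjects must not use statins, glucose lowering medication, or antioxidant dietary supplements 24 hours before the study testing". For at least 5 days before each admission, subjects also "must not use allergy or pain-related medicines".

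Phase 5 (Post-Intervention Testing) says only that the Phase 2 testing visits are repeated, and Phase 7 sends bariatric subjects back to earlier phases after surgery. Neither restates a medication rule. The notes under both visit schedules say that fitness and body-fat tests are done up to 3 days after the blood work.

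The walk test is one of two named fitness measures: Biomedical Research, item 1, lists "cardiorespiratory fitness (VO2max test, 6-minute walk test". Change in fitness between groups is item 6 of the outcomes under the primary objective. Statistical Considerations, item 4, adds paired t-tests for change within each treatment.

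**The concern.** Walk distance is compared before and after the intervention in the same subject. That comparison is clean only if the test conditions are the same on both occasions. Here the general restriction and the walk-test instruction point in different directions. The withholding rules for the metabolic visits add a third instruction, which can reach the follow-up walk test but not the baseline one. If a subject walks on usual medication at baseline and after withholding some of it at follow-up, the measured change contains both the intervention and the change in medication state. If this happens in some subjects and not others, it also adds scatter to small arms.

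**Working it through.** There is no figure in the plan to reproduce. The check sets the schedules beside the rules.

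| Walk test | Visit | Tolerance test in the same column | Rules that could apply |
|---|---|---|---|
| Baseline, both cohorts | 2 | none (it is at Visit 3) | walk-test sentence; general 24-hour bar |
| Post-intervention, bariatric | 4 (or 12) | MMTT | both of these, plus the Visits 3-6 rules |
| Post-surgery, bariatric | 6 (or 14) | MMTT | same |
| Post-intervention, non-bariatric | 18 (or 6) | OGTT | same |

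Exercising subjects attend the same testing visits under the numbers 12, 14 and 18. I take the Visits 3-6 rules to follow the tolerance test rather than the visit number.

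**Three readings are open.**

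1. The general 24-hour bar governs every test. Medication is then withheld at baseline and at follow-up. The conditions match, but the walk-test sentence is wrong.
2. The walk-test sentence governs every walk test, carried forward by Phase 5. The conditions match if the repeat walk is on a later day than the tolerance test. If it is on the same day, usual intake has already been interrupted for the withheld classes.
3. The walk-test sentence governs Visit 2, and the Visits 3-6 rules govern a same-day repeat. Medication is then as usual at baseline and partly withheld at follow-up.

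The text excludes none of the three. Because the schedule note allows 0 to 3 days between blood work and fitness tests, different subjects can fall under different readings.

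**Where a switch would show.** Let δ be the shift in walk distance caused by withholding, taken as equal in all switched subjects. Let p be the proportion of an arm that is switched.

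- Within an arm: expected observed change = true change + p × δ. This is what the paired t-test sees.
- Between arms E and C: expected distortion = (p_E − p_C) × δ, which is 0 when p_E = p_C.
- Added variance per subject: p(1 − p)δ². It is zero if nobody or everybody switches and positive in between.

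The protocol expects 12 bariatric and 24 non-bariatric completers (Human Participants, item 2). With an equal split, an arm has 12/2 = 6 or 24/2 = 12 subjects. One switched subject then moves the arm's mean change by δ/6 or δ/12. The document gives neither δ nor p, so this goes no further.

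**The case against.** The best defence is that the walk-test sentence is a test-specific instruction and naturally qualifies the general line. It is also permissive, so a subject who abstains breaks neither rule. The general line stands in a list that opens with drugs affecting insulin sensitivity or endothelial function, which suggests that the metabolic and vascular visits were meant. Visit 2 has its own preparation rule, a 4-hour fast, with no withholding. Phase 5 repeats the Phase 2 visits, which can be read as carrying the walk-test sentence forward, and a shared column in a schedule does not prove same-day testing.

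Much of this stands. The two sentences are not strictly impossible to obey together, and the protocol does not prescribe a switch. It does not close the gap, though. A permission leaves the medication state to each subject. Phase 5 names no medication rule. The schedule note allows the same day as well as a later one.

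A reader might also infer three stronger things that the document does not support.

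- **That the maximal exercise test is affected in the same way.** The permission appears only in the walk-test part. The part on the treadmill or cycle test gives no medication rule, so it states no on-medication baseline from which to switch.
- **That training intensity is affected.** The 65-85% heart-rate range is stated for the bariatric exercise arm and refers to a measured maximum heart rate. The walk-test sentence does not govern that measurement.
- **That the exercise effect itself is biased.** Within each comparison, both arms have the same visit timing and the same medication wording, so a common shift cancels.

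**Conclusion.** The point holds as a limited one. The medication instructions conflict or are left open for the walk test, and the text permits a switch from usual medication at baseline to partial withholding at follow-up in some subjects. The main exposure is in within-arm pre/post change and in precision. Between-arm bias would arise only if medication use or the spacing of test days differed by arm, and nothing in the document shows that they do.

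The size cannot be derived. It depends on how many subjects take a withheld drug, how many are tested on the same day as the tolerance test, and how far withholding shifts walk distance; the protocol gives none of these. Counting scheduled walk tests would not help, because a count ignores whether the subject takes any relevant drug. Item 3 also lists several drug classes as restricted without a time window, which makes the number exposed harder still to judge.

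The conclusion assumes that the Visits 3-6 rules apply wherever the tolerance test is done. I rate it as minor: worth correcting because it is cheap, not because it threatens the trial.

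**What to change.** Reconcile item 3 of the Inclusion/Exclusion Criteria, the Timed Walk Test part of Visit 2, the rules for Study Testing Visits 3-6, Phase 5, and the notes under the two visit schedules. The result should be one stated medication condition that applies at the baseline walk test and at every repeat. Which condition that is remains a clinical decision for the investigator. The text should also say how the condition is met when the walk test falls on the same day as the tolerance test.

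Record the last medication intake at each walk test, so that mismatched pairs can be identified and examined in a sensitivity analysis of the change in walk distance.

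The cost is protocol wording and one line on the test record, with no extra visit, procedure or subject.
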